#### Intervention: night shift

The goal of Night Shift is to teach physicians to recognize patients with ‘non-representative’ severe injuries, defined as injuries that are classified by the American College of Surgeons as life-threatening or critical, but that do not fit the archetype for injuries requiring treatment at a trauma center [4]. The intervention is designed to increase analogical encoding by having players experience a case that goes awry because of reliance on the representativeness heuristic, and providing specific feedback on relevant and irrelevant cues (i.e. ones they might have missed and ones that might have misled them). It is designed to facilitate narrative engagement by the providing the information in an emotionally compelling way. After considering different types of games (e.g. puzzles, role-playing), we decided that an adventure video game would provide an environment realistic enough for existing triage guidelines to appear valid, while including an element of fantasy to promote character identification and engagement.

Players take on the persona of Andy Jordan, a young emergency medicine physician who moves home after the disappearance of his estranged grandfather (Robert Jordan) and takes a job in the local emergency department (ED). The introduction tells players that they have two objectives. The first is to diagnose and treat patients who present to their ED. The second is to solve the mystery of Robert’s disappearance: was he murdered or has he chosen to disappear? [Fig. 2].

**Fig. 2 Fig2:**
[figure not shown]
Screen shots of trailer to Night Shift. Description of data: We show the trailer to the game. We provided players with two explicit objectives in order to heighten narrative engagement, while simultaneously providing a vehicle for physician education

The patients who present to the ED have both severe injuries and non-trauma complaints. In each case, subject physicians must interview the patients to elicit relevant elements of the history and physical exam. They then have the option of: a) ordering ancillary testing, b) discussing the case with a consultant, or c) discharging the patient home. Cases end when players make disposition decisions (admit, transfer, or discharge).

We categorize cases as ‘relevant’ or ‘non-relevant’ to our objective. ‘Relevant’ patients have non-representative severe injuries. When players fail to transfer one of these patients, he/she returns with complications that require additional treatment. Players also receive feedback on their performance from peers, family members, or their supervisor. The feedback includes both information about the clinical practice guidelines and a personal reprimand. In contrast, when players successfully transfer the patient to a trauma center, they receive an update, stating that the patient has improved, information about the guidelines, and a compliment on their diagnostic and decision-making capability.

‘Non-relevant’ patients either have representative severe injuries or non-trauma complaints. We included these cases because playtesters found that the ‘relevant’ cases did not pose sufficient diagnostic challenge, making game-play tedious. Players do not receive in-game feedback on their treatment of these patients. However, we do provide a summary of their performance at the end of *Night Shift*, which includes their ability to diagnose and treat the ‘non-relevant’ cases.

The mystery component of *Night Shift* occurs concurrently with the clinical challenges, and serves to facilitate players’ identification with their character and interest in their task. Players must solve Robert’s disappearance through interactions with other characters, including patients, and their physical environment. Andy Jordan’s background and character are also revealed through these interaction, which are designed to make him and his decisions more appealing and sympathetic [Table 1].

**Table 1 Tab1:** Description of *Night Shift*

Duration: Three hours of gameplay possible.	
Objective: To change physicians’ archetype of a representative severe injury	
Conceptual framework	
	• Highlight relevant contextual cues within the context of a narrative to facilitate integration into a mental model of the decision problem (analogical encoding).
	• Provide personally-relevant and emotionally-compelling feedback that increases retention of the message (narrative engagement)
Premise: The player takes on the role of Andy Jordan, a young emergency medicine physician, who moves home after his grandfather’s disappearance and accepts a job at a local community hospital covering night shifts.	
Content	
	Medical: Physicians interview patients who present to the Emergency Department, and have the option of investigating further, discussing the case with a consultant, or discharging the patient home. The patients include: • 5 deceptive trauma cases with severe injuries adapted from clinical practice. These patients have injuries classifed by the American College of Surgeons as ‘life-threatening or critical’ but that might appear minor. They return with complications if under-triaged, and allow the player to gain experience with relevant contextual cues and receive to feedback on performance. • 5 non-trauma cases adapted from the clinical case records of the Massachusetts General Hospital, presented in the New England Journal of Medicine. These patients serve as a diagnostic challenge to facilitate player engagement in the clinical task. • 2 obvious trauma cases with severe injuries adapted from clinical practice. These patients serve as a management challenge to facilitate player engagement in the clinical task.
	Non-medical: Robert Jordan, Andy’s estranged grandfather, has disappeared. The prologue hints that his disappearance may or may not have occurred voluntarily. The player must solve the mystery by uncovering clues revealed through conversation with in-game characters and by exploring the environment.
Game mechanics	
	1. Connect the dots: clues (medical and non-medical) appear on a notepad on the screen. The player can draw connections between clues to uncover information and to unlock additional dialogue options.
	2. Tap to act: the player can tap on the screen to move through the world and interact with other characters. This mechanic also allows the player to perform key patient-care actions, including procedures like lumbar punctures and intubations.
	3. Points: players receive points for uncovering non-medical clues, which unlock in-game lore. Specifically, they can access letters written by Andy and his grandfather, which should provide additional insight into their characters and motivations.

#### Intervention: educational control

The gold standard educational strategy in trauma is *Advanced Trauma Life Support (ATLS)*. The American College of Surgeons have developed ATLS, a 2-day seminar, to teach participants: to assess the patient’s condition rapidly and accurately; to resuscitate and to stabilize the patient; to determine if the patient’s needs exceeds the capabilities of their facility; to arrange for the definitive care of the patient, and to ensure that optimal care if provided. The course includes lectures on key topics (e.g. assessing the severity of the injury), instruction on skills relevant to the initial stabilization of the patient (e.g. putting in chest tubes), and practice using standardized patients. Participants must complete a multiple choice test before and after the course to receive certification [25].

We will use a two-part educational program as a surrogate. First, physicians review the *myATLS* app, designed and produced by the American College of Surgeons as an adjunct to the ATLS course [26]. The app includes a review of each chapter of the ATLS textbook, a series of videos demonstrating common trauma procedures, and clinical resources including checklists for use at the bedside. Second, physicians use the *Trauma Life Support MCQ Review*, an app designed to help students prepare for the ATLS exam. It includes 550 multiple-choice questions with correct answers and explanations. We will ask physicians to review the *myATLS* app and then complete questions in the *Trauma Life Support MCQ Review*, spending at least 1 h on the combined tasks.

### Data sources and management

#### Interventions

We will install *Centrify* on each iPad that we distribute, an app that tracks usage of programs, to measure how long physicians spend on their assigned apps (adherence). Data from this app will download daily to a secure server hosted by the University of Pittsburgh. In addition, the *Night Shift* application collects data on each player’s behaviors and actions (e.g. disposition decisions) during game-play. These data will be summarized using Google Analytics and then downloaded to the server.

#### Outcome assessment

After completing their assigned interventions, subjects will log into a website to complete a virtual simulation designed to replicate the task environment of an Emergency Department at a non-trauma center. The primary outcome of the clinical trial will be performance on the simulation, measured as the physician’s rate of under-triage (proportion of severely injured patients not transferred to a trauma center). We previously collaborated with a gaming company (Breakaway Ltd; [name]) to develop a 2-D simulation to assess physician decision making in trauma triage [Fig. 3]. The simulation has both internal reliability as well as construct validity [16]. Most importantly, in prior studies, we found that physicians make similar decisions for trauma patients on the simulation as they do in real-life. Performance on the virtual simulation will be transmitted from the website to a secure server hosted by the University of Pittsburgh.

**Fig. 3 Fig3:**
[figure not shown]
Screen shots of virtual simulation. Description of data: We show examples from the simulation. **a** Each case included a 2-D rendering of the patient, a chief complaint, vital signs, a history, and a written description of the physical exam. Physicians had 42 min (a simulated 8 h shift) to complete the ten cases. A clock at the top right of the screen helped track the passage of time. **b** Physicians could manage patients by selecting from a pre-specified list of 250 medications, studies, and procedures. **c** We included audio-visual distractors, including nursing requests for help with disruptive patients to increase the verisimilitude of the experience

The simulation has ten cases: three severely injured patients (one representative, two-non-representative), three minimally injured patients, and four non-trauma cases. Users must evaluate and manage these cases over 42 min, simulating a busy 8-h ED shift. New patients arrive at pre-specified (but unpredictable) intervals, so that physicians must manage multiple patients concurrently. Each case includes a 2-D rendering of the patient, a chief complaint, vital signs which update every 30 s, a history, and a written description of the physical exam. In the absence of clinical intervention by the player, severely injured patients and critically ill distractor patients decompensate and die over the course of the simulation.

Physicians manage patients by selecting from a pre-specified list of 250 medications, studies, and procedures. Some orders affect patients’ clinical status, leading to corresponding changes in their vital signs and physical exam. Other orders generate additional information, presented as reports added to the patients’ charts. The cases end when physicians either make a disposition decision (admit, discharge, transfer) or the patient dies.

There are two versions of the simulation: a control and a cognitive load condition. As mentioned earlier, cognitive load is expected to increase reliance on heuristics [24]. When poorly calibrated, these heuristics result in predictable errors. By varying cognitive load, we can assess the effect of the interventions on physicians’ heuristics (a secondary outcome measure). Specifically, a comparison of the difference in performance under control and cognitive load conditions of physicians in the two arms of the study will provide insight into the mechanism by which the interventions work. If physicians exposed to *Night Shift* demonstrate both lower under-triage rates, and less effect of cognitive load on performance, we can infer that *Night Shift* functions by recalibrating heuristics. In contrast, if physicians exposed to *Night Shift* perform better in general but have the same rate of errors when working under cognitive load as physicians exposed to the educational module, then we can infer that *Night Shift* functions through some alternative mechanism.

We operationalize cognitive load in two ways. First, we vary the complexity of the non-trauma cases. In the control arm, non-trauma cases have routine complaints (e.g. appendicitis), arrive hemodynamically stable, and do not deteriorate over the course of the simulation. In the cognitive load arm, non-trauma cases are critically ill (e.g. have sepsis), arrive hemodynamically unstable, and deteriorate without adequate management. Second, we reduce the number of rooms that physicians can use to evaluate patients, from eight in the control arm to four in the cognitive load arm, which increases the number of distractors that they receive.

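### Lower under-triage with a smaller load effect would not by itself show recalibrated heuristics, because only the game arm rehearses virtual ED cases ending in the outcome's own three dispositions

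*Protocol article*

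**What the plan says.** The mechanism rule is in the protocol article, Methods, Outcome assessment. If physicians in the game arm "demonstrate both lower under-triage rates, and less effect of cognitive load on performance, we can infer that" the game acts by recalibrating heuristics. The other branch covers game physicians who "perform better in general but have the same rate of errors when working under cognitive load as physicians exposed to the educational module"; the authors would then infer some other mechanism. The section calls the effect on heuristics a secondary outcome measure. The planned test is an ANOVA of each physician's under-triage rate on intervention, cognitive load and their interaction (Physician performance).

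The tasks are described as follows.

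- **Game** (Intervention: night shift, and Table 1): "Physicians interview patients who present to the Emergency Department, and have the option of investigating further". Also, "Cases end when players make disposition decisions (admit, transfer, or discharge".
- **Outcome** (Outcome assessment): participants "complete a virtual simulation designed to replicate the task environment of an Emergency Department at a non-trauma center". There, "The cases end when physicians either make a disposition decision (admit, discharge, transfer) or the patient dies".
- **Control** (Intervention: educational control): "The app includes a review of each chapter of the ATLS textbook, a series of videos demonstrating common trauma procedures, and clinical resources". A second app supplies 550 multiple-choice questions. No virtual case or disposition task is described for either app. The standardized-patient practice mentioned in that section belongs to the two-day ATLS course, not to its surrogate here.

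**The concern.** The arms differ in format as well as in theory. A physician who has just spent an hour or more working up virtual ED patients and choosing dispositions may handle another virtual ED more easily than one who has read chapters and answered questions. If that ease lowers under-triage and also softens the effect of load, both conditions of the positive branch are met without any change in the representativeness heuristic.

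At stake is what the trial may conclude about mechanism, which is hypothesis (b) and the reason for having two versions of the simulation. Familiarity with a format might also carry over less well to real triage than a recalibrated heuristic would.

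**Working it through.** **1. The plan's own figure.** The article gives an effect of 0.5 SD, alpha 0.05, power 80%, a 70% response rate and 366 recruits. A two-sample t-test, two-sided (sidedness is not stated), needs 63.8, so 64 per group. Four cells: 64 × 4 = 256, and 256 / 0.70 = 365.7, so 366. The figure reproduces. It matters here only as the source of 64 completers per cell, assuming that all who respond also finish.

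**2. The tasks side by side.** The game and the outcome share an ED setting, patient work-up, a mix of trauma and non-trauma cases, and the same three dispositions. The control shares none of these as described. The limitations in the Discussion name the two-arm design, the convenience sample and the unproven control, but not the shared format. The Discussion's remark that the control is similar in duration and complexity does not address format.

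**3. How familiarity could reach both signs.** The simulation gives 42 minutes for ten overlapping cases, and untreated severe patients die. Taken literally, the under-triage formula counts a severe patient who dies or is never dispositioned as not transferred, so handling efficiency can enter the outcome. Load is created by unstable non-trauma patients and by four rooms in place of eight, with more distractors. These are demands of the virtual ED itself, which practice on virtual ED cases could ease.

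**4. Illustration with zero recalibration.** From the article: three severe cases per physician. From step 1: 64 per cell. All else is assumed: control-arm rate without load b = 0.50 or 0.70; load effect L = 0.5 or 1.0 on the logit scale; familiarity gain f = 0.3 or 0.6; share s of the load effect removed by familiarity = 0, 0.5 or 1; within-physician correlation 0.2.

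- Control arm: logit(b) without load, logit(b) + L with load.
- Game arm: logit(b) − f without load, logit(b) − f + L(1 − s) with load.

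Example with b = 0.50, L = 1.0, f = 0.3, s = 0.5. The control arm goes from 0.500 to 0.731, a load effect of 23.1 points. The game arm goes from 0.426 to 0.550, a load effect of 12.4 points. The difference is 10.7 points, and both ANOVA tests were significant in the direction of the rule in 21% of 4,000 simulated trials.

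Across all settings:

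| Share of load effect removed (s) | Load effect smaller in game arm by | Both tests significant |
|---|---|---|
| 0 | −5 to 0 points | at most 3% |
| 0.5 | 3 to 11 points | 4% to 27% |
| 1 | 9 to 23 points | 18% to 81% |

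With s = 0 the main effect alone was significant in 31% to 94% of trials, but the interaction in at most 3%. The interaction therefore does screen out a practice gain that leaves the load effect alone. It does not screen out one that eases load.

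**The case against.** The strongest reply is that the rule already has a safeguard. A purely additive practice gain leaves the load effect no smaller, so the positive branch fails and the result falls on the side assigned to an alternative mechanism (reading that branch as an equal load effect, as its context suggests). The s = 0 row confirms this. The documents do not show that familiarity eases load; that step is an assumption. This stands, and it is why the point is conditional.

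A reader might infer that the game simply rehearses the outcome task. The documents do not support that. The game is an iPad adventure with tapping, clue-linking and a mystery plot, and no clock or concurrent patients are described for it. The outcome is a timed multi-patient website simulation with a 250-item order list. Participants are practising ED physicians, to whom disposition decisions are presumably not new. All this lowers the likely size of a format effect without removing it.

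It can also be said that case practice with feedback is the intervention's theory, that an ATLS-like comparator was a deliberate choice, and that a statistical analysis plan, not shown here, may hold further mechanism analyses. These are fair, and no format-matched arm is asked for. But the article itself fixes what may be inferred from the two signs. Nor would the adherence data it mentions settle the question, since more time in the game means more practice and more of the intended lesson. The Narrative Engagement Scale is given only to the game arm.

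**Conclusion.** The concern holds for the mechanism inference and no further. The positive branch accepts a pattern that recalibration predicts but that task familiarity could also produce, provided the familiarity eases load as well as lowering under-triage. The documents give no figure for such an effect. The ranges in the table show that the rule can be met without recalibration; they do not estimate how likely that is.

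A reader might go further and infer that the primary comparison is biased. It is not: the randomised difference in under-triage remains a valid effect of one whole package against the other, although part of any gain may come from format. Nor should the problem be sized by a shift in the main effect, because the rule also needs an arm-by-load difference. The sample size of 366 is unaffected.

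**What to change.** In Outcome assessment, weaken the positive branch so that the pattern would be consistent with recalibration, in place of permitting that inference. Then pre-specify two supportive specificity analyses of simulation data:

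1. Under-triage by arm and load, separately for the one representative and the two non-representative severe cases. Recalibration predicts a gain concentrated in the latter; general familiarity should help both.
2. Handling of the four non-trauma cases by arm: disposition reached within 42 minutes in both load conditions, and deaths in the load condition only. In the control condition these patients do not deteriorate, so deaths are uninformative there. The article says only that performance is transmitted, so confirm that these items are logged.

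Report both as estimates with confidence intervals. Do not require a null on the non-trauma cases: no margin exists, and better heuristics could themselves free attention for other patients.

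The cost is a little more analysis and limited precision. With one representative case per physician, 128 per arm and an assumed rate of 0.5, the standard error of the arm difference is √(2 × 0.25 / 128) = 0.0625, a 95% interval of about ±12 points. For the arm-by-load difference it is √(4 × 0.25 / 64) = 0.125, about ±25 points. If the representative case is seldom missed, there is also little room for it to improve. The non-trauma comparison is impure because the game contains five non-trauma cases of its own.

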**Methods:**

We developed *Night Shift* in collaboration with emergency medicine physicians, trauma surgeons, behavioral scientists, and game designers. Players take on the persona of Andy Jordan, an emergency medicine physician, who accepts a new job in a small town. Through a series of cases that go awry, they gain experience with the contextual cues that distinguish patients with minor and severe injuries (based on the theory of analogical encoding) and receive emotionally-laden feedback on their performance (based on the theory of narrative engagement). The planned study will compare the effect of *Night Shift* with that of an educational program on physician triage decisions and on physician heuristics. Psychological theory predicts that cognitive load increases reliance on heuristics, thereby increasing the under-triage rate when heuristics are poorly calibrated. We will randomize physicians (*n* = 366) either to play the game or to review an educational program, and will assess performance using a validated virtual simulation. The validated simulation includes both control and cognitive load conditions. We will compare rates of under-triage after exposure to the two interventions (primary outcome) and will compare the effect of cognitive load on physicians’ under-triage rates (secondary outcome). We hypothesize that: a) physicians exposed to *Night Shift* will have lower rates of under-triage compared to those exposed to the educational program, and b) cognitive load will not degrade triage performance among physicians exposed to *Night Shift* as much as it will among those exposed to the educational program.

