#### Physician performance

We hypothesize that: a) physicians exposed to *Night Shift* will have lower rates of under-triage compared to those exposed to the educational program, and b) cognitive load will not degrade triage performance among physicians exposed to *Night Shift* as much as it will among those exposed to the educational program.

To test these hypotheses, we will first score participants’ performance on each trauma case based on a review of their disposition decisions, using American College of Surgeons guidelines as the gold standard [4]. We will calculate an under-triage rate for each physician:$$ \frac{\mathrm{number}\ \mathrm{o}\mathrm{f}\ \mathrm{severely}\ \mathrm{injured}\ \mathrm{patients}\ \mathrm{not}\ \mathrm{t}\mathrm{ransferred}\ \mathrm{t}\mathrm{o}\ \mathrm{t}\mathrm{rauma}\ \mathrm{centers}}{\mathrm{total}\ \mathrm{number}\ \mathrm{o}\mathrm{f}\ \mathrm{severely}\ \mathrm{injured}\ \mathrm{patients}} $$

We will assess the influence of the intervention (game or educational program), cognitive load (absent or present), and the interaction between these factors on physicians’ under-triage rates using an ANOVA.

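### The rule for inferring recalibrated heuristics uses misses alone, so a large indiscriminate shift toward transfer could satisfy it

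*Protocol article*

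**What the plan says.** The Outcome assessment section of the protocol article takes simulation performance as the primary outcome, "measured as the physician’s rate of under-triage (proportion of severely injured patients not transferred to a trauma center". The simulation contains "three severely injured patients (one representative, two-non-representative), three minimally injured patients, and four non-trauma cases". Under Physician performance, the plan is to score "performance on each trauma case based on a review of their disposition decisions", which is six cases per physician. Only one rate is then derived, under-triage on the three severe cases. That rate is the only outcome of the ANOVA on intervention, load and their interaction. The article describes no rate that uses the three minimally injured cases.

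Outcome assessment also fixes how the result will be read. If Night Shift physicians "demonstrate both lower under-triage rates, and less effect of cognitive load on performance, we can infer that" the game acts by recalibrating heuristics. If they do better overall but make errors under load at the same rate as the education arm, some other mechanism is inferred.

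Table 1 lists the trauma content of the game as "5 deceptive trauma cases with severe injuries adapted from clinical practice" and "2 obvious trauma cases with severe injuries adapted from clinical practice"; the remaining five cases are non-trauma. The section on the Night Shift intervention says that failing to transfer one of the five relevant patients brings complications and a reprimand, and that transferring one brings good news and a compliment. Guideline information accompanies both.

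**The concern.** A miss rate mixes two things: how well a physician tells severe from minor injury, and how ready that physician is to transfer anyone. Only the first is recalibration in the sense the article intends. The inference rule sees only misses, so it cannot separate the two when the change in readiness is large.

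The rival explanation is not far-fetched. All the trauma patients in the game are severely injured, and feedback on the relevant cases always favours transfer. A player could come away with a lower threshold for every trauma patient. A blanket rule also takes little thought, so resistance to load is what one would expect from it. At stake is the trial's mechanistic conclusion, and the reading of fewer misses as better triage.

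**Working it through.** **1. Cell size.** The power section gives 0.5 SD, alpha 0.05, 80% power, a 70% response rate and 366 physicians. A two-sample t-test (two-sided, assumed) needs 64 per group. With four cells, 4 × 64 = 256 and 256 / 0.70 = 365.7, rounded up to 366, which reproduces the figure. Two groups alone would give 128 / 0.70 = 182.9, or 183. I use 64 per cell in step 4 only. This treats the 70% as completion, whereas Analyses defines response as starting the intervention.

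**2. Extreme case: every trauma patient transferred.**
- Under-triage = severe not transferred / 3 = 0/3 in control and 0/3 under load, so the load effect is 0.
- Over-triage = minimally injured transferred / 3 = 3/3 in both conditions.
- Severe minus minimal transfer rate = 1 − 1 = 0, so there is no discrimination at all.

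Both conditions of the rule hold in expectation whenever load raises under-triage in the education arm, as the article predicts.

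**3. Partial shifts with discrimination held constant.** Illustrative model (all inputs assumed): severe cases produce a signal distributed N(d′, 1), minimal cases N(0, 1), and the physician transfers if the signal exceeds c. Then under-triage = Φ(c − d′) and over-triage = 1 − Φ(c). I take d′ = 1 and education-arm under-triage of 60% without load, so c = 1 + 0.253 = 1.253. Load raises c by 0.4. The game lowers c by the shift shown and leaves d′ alone. Pairs are control / load.

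| Shift (SD) | Under-triage | Load effect | Over-triage | Severe − minimal transfer rate |
|---|---|---|---|---|
| 0 (education) | 0.600 / 0.743 | 0.143 | 0.105 / 0.049 | 0.295 / 0.208 |
| 0.5 | 0.403 / 0.561 | 0.158 | 0.226 / 0.124 | 0.371 / 0.315 |
| 1 | 0.228 / 0.364 | 0.137 | 0.400 / 0.257 | 0.372 / 0.379 |
| 2 | 0.040 / 0.089 | 0.049 | 0.772 / 0.636 | 0.188 / 0.275 |

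The last column is (1 − under-triage) − over-triage; for example, at 2 SD in control, 0.960 − 0.772 = 0.188.

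At 2 SD both conditions are met with no gain in d′. At 0.5 to 1 SD under-triage falls but the load effect stays at 14 to 16 points, so the second condition is not met. With d′ = 0.5 or 1.5 the under-triage columns are identical. At 2 SD over-triage is then 89%/80% or 60%/44%.

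**4. Would both effects be detected?** Simulated 2 × 2 ANOVA: 64 per cell, three severe cases each, physician SD 0.5 on the logit scale, education-arm under-triage of 40% to 75% without load, blanket transfer in the game arm. The main effect is significant in essentially every trial. Main effect and interaction together are significant in:
- 14–20% of trials if load adds 5 points in the education arm
- 44–64% if it adds 10 points
- 76–96% if it adds 15 points
- 95–100% if it adds 20 points

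**5. Game content.** Table 1 gives 5 + 2 = 7 trauma cases, all severe, plus 5 non-trauma cases, 12 in total. No minor-injury case is listed.

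**The case against.** Four objections carry weight.

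*The article may be condensed.* All six trauma cases are scored, and a further secondary outcome could sit in a full protocol or SAP that is not shown. That is fair: the absence of an over-triage outcome is not in itself the point. The point is the inference rule, which the article states in full and rests on under-triage alone.

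*The rule already screens out some threshold shifts.* This is correct for modest ones, as step 3 shows. A reader might infer that any drift toward transfer would be declared recalibration. The documents do not support that. It takes a large or total shift, together with a load effect in the education arm big enough to detect.

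*Blanket transfer is conjecture.* Nothing in the article says physicians will learn it, and feedback also conveys the guidelines. That stands. The game's content makes such a shift plausible, not likely, and a rule for inferring mechanism should still be able to exclude it.

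*The hypotheses concern under-triage.* They do, and the stated problem is under-triage too. A reader might infer that the primary outcome is invalid. It is not: the between-arm comparison of under-triage answers the question it poses.

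A reader might also see a contradiction between the abstract, where players "they gain experience with the contextual cues that distinguish patients with minor and severe injuries", and a game with no minor-injury cases. The abstract speaks of cues, not of case mix, and Table 1 says the deceptive injuries may look minor. No correction of the abstract is called for.

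**Conclusion.** The concern holds for the mechanistic inference. As written, the rule cannot tell recalibration from a large indiscriminate move toward transfer. Blanket transfer scores 0/3 under-triage in both load conditions and 3/3 over-triage, and would satisfy both conditions in expectation. In the illustrative model a 2 SD shift with constant discrimination does much the same.

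The extreme case follows from the outcome definition and needs only that load worsens under-triage in the education arm. The partial-shift figures rest on an assumed d′, base rate and load effect. The detection probabilities, 14% to 100%, rest on the assumed load effect and 64 completers per cell. The primary comparison, its analysis and data collection are unaffected.

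**What to change.** - From the cases already scored, calculate an over-triage rate for each physician: minimally injured patients transferred / 3.
- Analyse that rate, and the difference in transfer rate between severe and minimally injured cases, as secondary outcomes in the same intervention-by-load model.
- Reword the rule in Outcome assessment so that recalibration is inferred only if the fall in under-triage comes with better discrimination and is not explained by a matching rise in over-triage.

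The two new measures should be read together, because the difference in rates is not free of the threshold. In step 3, averaged over load, it moves from (0.295 + 0.208)/2 = 0.25 to (0.372 + 0.379)/2 = 0.38 for a 1 SD shift with d′ unchanged, while over-triage rises from 11%/5% to 40%/26%. Per-physician d′ is not required: with three cases of each kind it is undefined at 0/3 or 3/3 unless a correction is applied.

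The cost is one or two more secondary analyses and a more cautious statement about mechanism. No new data are needed. The change should be fixed before group assignment is unmasked.
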